### Expected toxicities and management

Toxicity will be graded using CTCAE version 5.0, and treatment criteria will be evaluated prior to each cycle (Table 2). Participants will be followed for up to 3 years or until death, whichever occurs first. Participants removed from protocol therapy for unacceptable adverse event(s) will be followed until resolution or stabilization of the adverse event. Survival status will be checked every 6 months during that time. Participants removed from study for unacceptable adverse events will be followed until resolution or stabilization of the adverse event. Expected toxicities from cisplatin include nausea, diarrhea, nephrotoxicity, tinnitus, ototoxicity, neutropenia, and thrombocytopenia. In the cases of grade 3 or 4 nausea, cisplatin would be held, and dose reduced (Table 3). Commonly seen adverse events seen with pembrolizumab include immune-mediated pneumonitis, colitis, hepatitis, hypophysitis, hypo/hyperthyroidism, thyroiditis, type 1 diabetes mellitus, nephritis and rashes including; Stephens-Jonson syndrome (SJS) and Toxic epidermal necrolysis (TEN). Similarly, management outlines for neutropenia and thrombocytopenia are also shown in Table 3. In the event of suspected or confirmed immune-related adverse events (irAEs) attributed to pembrolizumab, guidelines for management are detailed in Table 4. Adverse events from radiation therapy include rashes, wounds, and other cutaneous manifestations, dysuria, and diarrhea.

**Table 2 Tab2:** Treatment criteria for the first cycle and subsequent cycles

Cycle 1 criteria	Subsequent cycles
Absolute neutrophil count ≥ 1500/mcL Platelets ≥ 100,000/mcL Hemoglobin ≥ 9 g/dL Total bilirubin ≤ 1.5 × institutional upper limit of normal AST (SGOT)/ALT (SGPT) ≤ 2.5 × institutional upper limit of normal Creatinine ≤ 1.5 × ULN or creatinine clearance ≥ 50 mL/min for subjects with creatinine levels above institutional ULN All toxicities of previous therapy (aside from alopecia) must have resolved to ≤ grade 1 ECOG performance of 0 or 1 No evidence of life-threatening medical problems	Absolute neutrophil count ≥ 500/mcL Platelets ≥ 50,000/mcL AST (SGOT)/ALT (SGPT) ≤ 2.5 × institutional upper limit of normal Creatinine ≤ 1.5 × ULN or creatinine clearance ≥ 50 mL/min for subjects with creatinine levels above institutional ULN All toxicities of previous cycles must have resolved to ≤ grade 2 ECOG performance of 0 to 2 No evidence of life-threatening medical problems

*ULM* upper limit of normal

**Table 3 Tab3:** Toxicity and treatment holds

	Management/next dose for cisplatin	Management/next dose for pembrolizumab
Nausea/vomiting		
≤ Grade 1	No change in dose	No change in dose
Grade 2	No change in dose	No change in dose
Grade 3	Hold^a^ until < Grade 2. Resume at one dose level lower, if indicated.	No change in dose^b,c^
Grade 4	Hold^a^ until < Grade 2. Resume at two dose levels lower.	No change in dose^b,c^
Diarrhea		
≤ Grade 1	No change in dose	No change in dose
Grade 2	No change in dose	No change in dose
Grade 3	Hold^a^ until < Grade 2. Resume at one dose level lower, if indicated	No change in dose^b,c^
Grade 4	Hold^a^ until < Grade 2. Resume at two dose levels lower	No change in dose^b,c^
Neutropenia		
≤ Grade 1	No change in dose	No change in dose
Grade 2	No change in dose	No change in dose
Grade 3	No change in dose	No change in dose
Grade 4	Hold^d^ until < Grade 3. Resume at current dose.	Hold until ≤ Grade 2
Thrombocytopenia		
≤ Grade 1	No change in dose	No change in dose
Grade 2	No change in dose	No change in dose
Grade 3	Hold^d^ until < Grade 2. Resume at same dose level	No change in dose
Grade 4	Hold^d^ until < Grade 2. Resume at same dose level	Hold until ≤ Grade 2

^a^Participants requiring a delay of > 2 weeks should go off protocol therapy

^b^Please see pembrolizumab adverse event management in Table 4

^c^As long as AE is unrelated to Pembrolizumab

^d^Participants requiring a delay of > 4 weeks should go off protocol therapy

**Table 4 Tab4:** Pembrolizumab toxicity and management

Immune related Adverse Events (irAEs)	Toxicity grade (CTCAE V5.0)	Action with pembrolizumab	Corticosteroid and/or other therapies	Monitoring and follow-up
Pneumonitis	Grade 2	Withhold	Administer corticosteroids (initial dose of 1–2 mg/kg prednisone or equivalent) followed by taper Add prophylactic antibiotics for opportunistic infections	Monitor participants for signs and symptoms of pneumonitis Evaluate participants with suspected pneumonitis with radiographic imaging and initiate corticosteroid treatment
	Grade 3 or 4, or recurrent Grade 2	Permanently discontinue		
Diarrhea/Colitis	Grade 2 or 3	Withhold	Administer corticosteroids (initial dose of 1–2 mg/kg prednisone or equivalent) followed by taper	Monitor participants for signs and symptoms of enterocolitis (i.e., diarrhea, abdominal pain, blood or mucus in stool with or without fever) and of bowel perforation (i.e., peritoneal signs and ileus) Participants with ≥ Grade 2 diarrhea suspecting colitis should consider GI consultation and performing endoscopy to rule out colitis Participants with diarrhea/colitis should be advised to drink liberal quantities of clear fluids. If sufficient oral fluid intake is not feasible, fluid and electrolytes should be substituted via IV infusion
	Grade 4 or recurrent Grade 3	Permanently discontinue		
AST or ALT elevation or Increased Bilirubin	Grade 2^a^	Withhold	Administer corticosteroids (initial dose of 0.5–1 mg/kg prednisone or equivalent) followed by taper	Monitor with liver function tests (consider weekly or more frequently until liver enzyme value returned to baseline or is stable)
	Grade 3^b^ or 4^c^	Permanently discontinue	Administer corticosteroids (initial dose of 1–2 mg/kg prednisone or equivalent) followed by taper	
Type 1 diabetes mellitus (T1DM) or Hyperglycemia	New onset T1DM or Grade 3 or 4 hyperglycemia associated with evidence of β–cell failure	Withhold^d^	Initiate insulin replacement therapy for participants with T1DM Administer anti-hyperglycemic in participants with hyperglycemia	Monitor participants for hyperglycemia or other signs and symptoms of diabetes
Hypophysitis	Grade 2	Withhold	Administer corticosteroids and initiate hormonal replacements as clinically indicated	Monitor for signs and symptoms of hypophysitis (including hypopituitarism and adrenal insufficiency)
	Grade 3 or 4	Withhold or permanently discontinue^d^		
Hyperthyroidism	Grade 2	Continue	Treat with non-selective beta-blockers (e.g., propranolol) or thionamides as appropriate	Monitor for signs and symptoms of thyroid disorders
	Grade 3 or 4	Withhold or permanently discontinue^d^		
Hypothyroidism	Grade 2, 3, or 4	Continue	Initiate thyroid replacement hormones (e.g., levothyroxine or liothyronine) per standard of care	Monitor for signs and symptoms of thyroid disorders
Nephritis and renal dysfunction: grading according to increased creatinine or acute kidney injury	Grade 2	Withhold	Administer corticosteroids (prednisone 1–2 mg/kg or equivalent) followed by taper	Monitor changes of renal function
	Grade 3 or 4	Permanently discontinue		
Myocarditis	Grade 1 or 2	Withhold	Based on severity of AE administer corticosteroids	Ensure adequate evaluation to confirm etiology and/or exclude other causes
	Grade 3 or 4	Permanently discontinue		
All Other immune-related AEs	Intolerable/persistent Grade 2	Withhold	Based on severity of AE administer corticosteroids	Ensure adequate evaluation to confirm etiology or exclude other causes
	Grade 3	Withhold or discontinue based on the event^e^		
	Grade 4 or recurrent Grade 3	Permanently discontinue		

^a^ AST/ALT: > 3.0–5.0 × ULN if baseline normal; > 3.0–5.0 × baseline, if baseline abnormal; bilirubin: > 1.5–3.0 × ULN if baseline normal; > 1.5–3.0 × baseline if baseline abnormal

^b^ AST/ALT: > 5.0 to 20.0 × ULN, if baseline normal; > 5.0–20.0 × baseline, if baseline abnormal; bilirubin: > 3.0–10.0 × ULN if baseline normal; > 3.0 × 10.0 × baseline if baseline abnormal

^c^ AST/ALT: > 20.0 × ULN, if baseline normal; > 20.0 × baseline, if baseline abnormal; bilirubin: > 10.0 × ULN if baseline normal; > 10.0× baseline if baseline abnormal

^d^ The decision to withhold or permanently discontinue pembrolizumab is at the discretion of the investigator or treating physician. For participants with Grade 3 or 4 immune-related endocrinopathy where withhold of pembrolizumab is required, pembrolizumab may be resumed when AE resolves to ≤ Grade 2 and is controlled with hormonal replacement therapy or achieved metabolic control (in case of T1DM)

^e^ Events that require discontinuation include but are not limited to: Guillain–Barre Syndrome, encephalitis, Stevens-Johnson Syndrome and toxic epidermal necrolysis

Severe diarrhea could be from cisplatin, radiation, or pembrolizumab, and precise attribution might be challenging in some cases. To prevent patients receiving definitive therapy from unnecessary treatment breaks and delays due to suspected superimposed immune-related colitis, the first three patients with locally advanced/unresectable disease will get pembrolizumab on cycle 1 day 1 and omit further pembrolizumab until cycle 4 day 1. If no unexpected toxicities are seen, all remaining patients in this category will receive pembrolizumab uninterrupted every 3 weeks.

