## Methods

### Aim and study design

The purpose of this study is to capitalize on the immunogenic properties of concurrent cisplatin/radiation via addition of pembrolizumab. Addition of pembrolizumab to cisplatin-sensitized radiation (Cis-RT) therapy is hypothesized to increase overall response rate, and recurrence free survival via increased cytotoxic T-cell engagement and activation. Based on this hypothesis, immunotherapy would need to be given concurrently with Cis-RT. Unlike CTLA-4 inhibitors, pembrolizumab has not been shown to have a dose-dependent relationship to toxicity with the currently utilized dose of 200 mg/m^2^ every 3 weeks. Due to this, a phase 1 trial with varying doses of pembrolizumab would not be instructive regarding toxicity and would likely impact potential efficacy. Also, due to the long half-life and frequency of administration, to test the hypothesis of synergy outlined in this study, pembrolizumab has to be present when Cis-RT is given. This makes a phase 2 trial design with pembrolizumab lead-in less ideal. In light of this, we decided to pursue a single-arm phase 2 clinical trial of concurrent Cis-RT and pembrolizumab. Finally, published and emerging toxicity data from immunotherapy plus chemoradiation combinations in other solid tumors have been reassuring, as described in the discussion section. The first three (3) patients with locally advanced or unresectable disease will receive cycle 1 of pembrolizumab followed by a break and resumption of pembrolizumab at cycle 4 and as part of a safety cohort. These patients will receive a total of 10 cycles of pembrolizumab (Fig. 1). All other patients, including the fourth patient with locally advanced/unresectable disease, will receive weekly cisplatin and pembrolizumab every 3 weeks, concurrently with daily radiation therapy (Fig. 2). Following completion of Cis-RT, patients will continue pembrolizumab maintenance for a total of 10 cycles in the safety cohort or 12 cycles for all other participants. Archived tissue will be used for MSI, PD-L1 and TIL stratification post hoc. Imaging will be performed at baseline and every 3 cycles (21-day cycles) as per standard-of-care. Laboratory analysis will occur on the first day of each cycle. We will collect and evaluate HPV status, PD-L1, and MSI status prior to therapy, but this will not be used for eligibility. Radiographic imaging will be performed every 9 weeks and overall response rate will be determined by RECIST 1.1 criteria.

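### Tables 2, 3 and 4 give conflicting continue and withhold rules for pembrolizumab, and the protocol does not say which table governs

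*Protocol article*

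**What the plan says.** All three tables stand in the protocol article under Expected toxicities and management.

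- **Table 2** lists the criteria checked before each cycle. For cycles after the first, one line reads "All toxicities of previous cycles must have resolved to ≤ grade 2". It is not split by drug or by cause. The same column also sets blood-count limits: "Absolute neutrophil count ≥ 500/mcL Platelets ≥ 50,000/mcL".
- **Table 3** gives separate cisplatin and pembrolizumab actions for nausea/vomiting, diarrhea, neutropenia and thrombocytopenia. The pembrolizumab entry for grade 2 diarrhea is "No change in dose", with no footnote. For grade 3 and 4 nausea/vomiting and diarrhea the entry is the same but carries footnote b, which points to Table 4, and footnote c: "As long as AE is unrelated to Pembrolizumab". For grade 3 thrombocytopenia, pembrolizumab is unchanged with no footnote.
- **Table 4** gives the action by immune-related event. It withholds pembrolizumab for diarrhea/colitis at grade 2 or 3, and continues it for hypothyroidism at grades 2 to 4. The text introducing it confines it to suspected or confirmed immune-related events attributed to pembrolizumab.

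Nothing in the section says which table prevails when two of them differ.

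**The concern.** For the same toxicity and grade, a clinician can reach opposite pembrolizumab decisions depending on the table consulted. The conflict runs both ways: at grade 2 diarrhea, Table 3 continues where Table 4 withholds; at grades 3 and 4, Tables 3 and 4 let pembrolizumab go on where Table 2 does not let the cycle start.

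Patient safety is the first thing at stake. Diarrhea is the toxicity the protocol itself singles out: the modified schedule for the first three locally advanced patients exists because severe diarrhea could come from cisplatin, radiation or pembrolizumab and may be hard to attribute. The second is interpretation. With 24 patients, inconsistent holds would make exposure, discontinuations and toxicity rates hard to read.

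**Working it through.** The plan gives no figure on this point, so the check sets the tables side by side. "Admitted" means that Table 2's general toxicity line lets the next cycle start.

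| Toxicity, grade | Table 2 | Table 3, pembrolizumab | Table 4, pembrolizumab |
|---|---|---|---|
| Diarrhea, 2 | admitted | unchanged, no condition | withheld |
| Diarrhea, 3 | not admitted | unchanged if unrelated | withheld; stopped if recurrent |
| Diarrhea, 4 | not admitted | unchanged if unrelated | stopped |
| Nausea/vomiting, 3 and 4 | not admitted | unchanged if unrelated | no row of its own |
| Thrombocytopenia, 3 | not admitted | unchanged | no row of its own |
| Hypothyroidism, 3 and 4 | not admitted | no row | continued |

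**Grade 2 diarrhea.** Tables 3 and 4 differ. Table 3 uses footnotes b and c to separate pembrolizumab-related from unrelated events, but only at grades 3 and 4. Leaving them off the grade 2 row makes that row read as unconditional.

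**Grade 3–4 diarrhea.** Here the footnotes do settle Table 3 against Table 4. They do not settle it against Table 2, which makes no exception for unrelated events.

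**Nausea/vomiting, thrombocytopenia, hypothyroidism.** In each case the drug-specific table lets pembrolizumab proceed at a grade that Table 2 excludes. For grade 3 thrombocytopenia, Table 3 holds cisplatin but not pembrolizumab, a split that Table 2 does not recognize.

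**Count.** The pembrolizumab column of Table 3 has 4 toxicities × 4 grade rows = 16 entries. Those that differ from another table are diarrhea grade 2 (1), diarrhea grades 3–4 (2), nausea/vomiting grades 3–4 (2) and thrombocytopenia grade 3 (1): 1 + 2 + 2 + 1 = 6 of 16. Hypothyroidism adds two grades from Table 4.

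**Neutropenia, conditional.** The article gives no grade cut-points for neutrophils. Assume that 500 to <1000/mcL is grade 3. Table 2's neutrophil line then admits grade 3, in agreement with Table 3, while Table 2's own general line excludes it, so the conflict lies inside Table 2. If instead every count of 500/mcL or more were grade 2 or lower, Table 2 would be consistent with itself, but Table 3's unchanged dose at grade 3 would then differ from it. Because its place depends on the cut-points, this item is kept out of the count; including it gives 7 of 16.

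**Primary endpoint.** As a side check, the rule of 12 or more responses in 24 gives Σ C(24,k) p^k (1−p)^(24−k) over k = 12 to 24. This is 0.0314 at p = 0.30 and 0.886 at p = 0.60, in line with the stated 89% power at a 0.05 level. No input to that calculation comes from Tables 2 to 4.

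**The case against.** The strongest defense is that the tables have different scopes. Table 4 covers suspected or confirmed immune-related events, and its monitoring text for diarrhea speaks of grade 2 or higher with suspected colitis. Table 3 would then cover everything else. This is a sensible reading and it softens the grade 2 diarrhea conflict. It does not remove it, because Table 3 writes the attribution condition on the neighboring rows and omits it at grade 2. The protocol's remark on difficult attribution concerns severe diarrhea, so it supports the point only in part.

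A second defense is that Table 2 is a minimum condition to which the other tables add restrictions. That works wherever Table 2 is the more permissive table. It cannot explain the entries where Tables 3 and 4 allow what Table 2 excludes. One could reply that an unchanged dose in Table 3 fixes only the dose and leaves timing to Table 2. But Table 3 states its own holds where it wants them, and Table 4's instruction for hypothyroidism is to continue.

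Several stronger readings are tempting but unsupported:

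- **That Table 2 contradicts Table 4 in every immune-related category withheld at grade 2.** A minimum condition and an added restriction can both be obeyed. For transaminases with a normal baseline, Table 4's grade 2 range ("AST/ALT: > 3.0–5.0 × ULN if baseline normal") already fails Table 2's limit ("AST (SGOT)/ALT (SGPT) ≤ 2.5 × institutional upper limit of normal"), and Table 2's creatinine line may bar some nephritis.
- **That values between 2.5 and 3.0 × ULN are a contradiction.** A cycle limit and a higher threshold for immune-related action can both be followed.
- **That weekly cisplatin lacks blood counts.** The article says "Laboratory analysis will occur on the first day of each cycle"; it does not say that no other samples are taken. A condensed article may leave the full schedule to the protocol, and cisplatin-radiation is given as standard of care.
- **That local centers would apply different pembrolizumab rules.** The abstract places pembrolizumab and adverse event monitoring at a centralized site.

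**Conclusion.** The point holds as an internal inconsistency. Six of 16 pembrolizumab entries in Table 3 and two hypothyroidism grades in Table 4 differ from another table, with no order of precedence. One further inconsistency, over neutropenia, depends on grade cut-points that the article does not give.

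The finding rests on reading Table 2's general toxicity line as written, for all drugs and causes, and Table 3's grade 2 diarrhea row as unconditional because it carries no footnote. A scope statement or precedence rule in the full protocol could resolve much of it, but the tables as printed do not.

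The weight of the point is in patient safety and consistent exposure. Its effect on dose intensity or toxicity rates cannot be quantified from the article. The sample size, power and decision rule for overall response rate stand.

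**What to change.** The clinical team must:

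1. reconcile Tables 2, 3 and 4 so that each toxicity and grade has one rule per drug;
2. state which table governs where they differ, and whether Table 2's general toxicity line applies to each drug separately and to events of any cause;
3. state whether footnotes b and c of Table 3 also cover grade 2 diarrhea;
4. reconcile Table 2's neutrophil line with its general toxicity line, giving the grade cut-points used.

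This review takes no view on which rule is right. The cost is a protocol clarification or amendment sent to those treating patients, with no change to sample size or analysis.

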Lastly, immunotherapy maintenance after immunogenic interventions such as local ablative therapy or radiation therapy has been shown to be beneficial. For instance, patients with non-small cell lung (NSCLC) cancer treated with maintenance pembrolizumab after ablative therapy on a phase 2 study demonstrated statistically significant improvement in progression free survival (PFS) compared to historic controls [25]. In another report by Bersanelli et al. [26], patients who revived concurrent immunotherapy with radiotherapy had a longer PFS compared to patients who received radiation alone. A randomized placebo-controlled phase 3 trial evaluated the role of maintenance durvalumab in patients with NSCLC who had received chemoradiotherapy and found significant improvements in overall response rate, 12-month PFS, 18-month PFS and duration of response [27]. Notably, these combinations were well-tolerated.

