## Discussion

There are numerous clinical trials that support safety of the combination of chemotherapy with immune checkpoint blockade [31–33]. In addition, there is prospective safety data for combining chemoradiation with immune checkpoint blockade. Phase 2 and 3 clinical trials in NSCLC evaluating concurrent platinum-based chemotherapy with RT and PD-L1 blockade reported an incidence of about 30% in adverse related events [27, 34]. This is not significantly higher than what would be expected for chemoradiation treatment alone. A phase 1 trial by Tang et al. evaluated the combination of hypofractionated radiotherapy; 50 Gy in 4 fractions or 60 Gy in 10 fractions, with ipilimumab in patients with metastatic solid tumor malignancies [35]. In this study, 34% of patients developed grade 3 toxicity with colitis being the most common adverse event. Of note, 23% of the patients treated on this trial derived benefit via abscopal effects [35]. Another phase I trial combined pembrolizumab with various courses of radiation therapy; 30 Gy in 3 fractions for osseous metastasis, 50 Gy in 5 fractions for central lung tumors and 45 Gy in 3 fractions for other sites [36]. Only 6% of the 62 participants in this trial experienced grade 3 toxicities. The authors also reported abscopal effects in 13.2% of these patients [36]. NRG-GY017 is an ongoing phase I clinical trial evaluating an anti-PD-L1 inhibitor, atezolizumab, in patients with node positive Stage IB2, II, IIIB, or IVA cervical cancer. Similar to this trial, both arms of the study include the administration of immune checkpoint blockade concurrently with cisplatin-sensitized radiation therapy at doses similarly used for GYN malignancies, and there have been no adverse safety signals reported (NCT 03738228). As a safety precaution, the first three patients with locally advanced unresectable disease treated on this trial with receive pembrolizumab on cycle 1 and then resume on cycle 4 and on (Fig. 1).

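### The release condition for the three-patient safety cohort conflicts with the unconditional wording elsewhere, does not clearly cover the toxicity given as its reason, and rests on a schedule with fewer concurrent pembrolizumab doses than the one released

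*Protocol article*

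**What the plan says.** The first three patients with locally advanced or unresectable disease form a safety cohort. They receive pembrolizumab at cycle 1, omit cycles 2 and 3, and resume at cycle 4 after chemoradiation, for 10 cycles in total against 12 for other patients (Aim and study design; Study procedures; Expected toxicities and management).

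The reason is given in the text after Table 4: "Severe diarrhea could be from cisplatin, radiation, or pembrolizumab, and precise attribution might be challenging in some cases". The stated aim is to spare patients on definitive treatment from breaks and delays caused by suspected immune-related colitis. The release condition follows: "If no unexpected toxicities are seen, all remaining patients in this category will receive pembrolizumab uninterrupted every 3 weeks".

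Earlier in the same section, the article says "Expected toxicities from cisplatin include nausea, diarrhea, nephrotoxicity" and "Commonly seen adverse events seen with pembrolizumab include immune-mediated pneumonitis, colitis, hepatitis". It also lists diarrhoea as an adverse event of radiation. None of these lists carries a grade. Table 3 has rows for grade 3 and grade 4 diarrhoea, and Table 4 has rows for diarrhoea/colitis from grade 2 to grade 4.

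Aim and study design states: "All other patients, including the fourth patient with locally advanced/unresectable disease, will receive weekly cisplatin and pembrolizumab every 3 weeks". The Abstract says the same, and Study procedures puts all other patients on concurrent treatment throughout. None of the three mentions a condition.

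**The concern.** There are three difficulties with one safety rule.

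- **Conditional or not.** One section makes the uninterrupted schedule depend on what happens in the first three patients, and three others do not. A site enrolling the fourth locally advanced patient cannot tell from the text whether an assessment has to come first.
- **What counts.** The rule turns on *unexpected* toxicity, but the events that motivate the cohort are the ones the article presents as expected, common or already provided for.
- **What a clean result shows.** The three patients do not receive the schedule that a clean result releases.

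At stake is whether severe bowel toxicity in the cohort would bear on the decision to release, and whether a clean cohort might later be cited as evidence of tolerability for a schedule that none of the three received.

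**Working it through.** **Plan's own figures.** The article gives no operating characteristic for the safety cohort. Its only power figure is for overall response rate (ORR): n = 24, reject at 12 or more responses, 30% against 60%. An exact binomial calculation gives power 0.886 (stated as 89%) and attained one-sided alpha 0.031. That figure is correct and this point does not affect it.

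**Step 1: the condition across sections.**

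| Section | Schedule for patients after the first three | Condition |
|---|---|---|
| Abstract, Methods | Concurrent; fourth patient named | None |
| Aim and study design | Concurrent; fourth patient named | None |
| Study procedures | Concurrent throughout | None |
| Expected toxicities and management, after Table 4 | Uninterrupted, every 3 weeks | No unexpected toxicities |

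**Step 2: the criterion against its reason.** The reason is severe diarrhoea and suspected colitis. Diarrhoea is called expected for cisplatin and is listed for radiation. Colitis is called commonly seen for pembrolizumab, under a section heading about expected toxicities. The severe grades have their own rows in Tables 3 and 4. If *unexpected* means not on these lists, any count of such events from 0/3 to 3/3 satisfies the rule.

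**Step 3: dose timing.** Inputs: 32–38 fractions, 5 per week (Study procedures), and 21-day cycles, so pembrolizumab days are 1, 22, 43 and 64. Assumption: radiation starts on a Monday, cycle 1 day 1, and runs without breaks.

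- 32 fractions: six full weeks (30 fractions, 42 days) plus 2 fractions, so the last day is 42 + 2 = 44.
- 38 fractions: seven full weeks (35 fractions, 49 days) plus 3 fractions, so the last day is 49 + 3 = 52.

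Days 1, 22 and 43 fall within radiation in both cases, and day 64 falls after it. The cohort receives day 1 and omits days 22 and 43, which is 2 of the 3 concurrent doses. The totals agree: 12 − 2 = 10.

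**Step 4: what 0 of 3 could show if such events did count.** P(0 of 3) = (1 − p)³. The rates p are assumptions, because the article gives none for this combination.

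| Assumed true rate | P(0 of 3) |
|---|---|
| 10% | 0.9³ = 0.73 |
| 20% | 0.8³ = 0.51 |
| 30% | 0.7³ = 0.34 |
| 40% | 0.6³ = 0.22 |

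The exact one-sided 95% upper limit for 0/3 is 1 − 0.05^(1/3) = 0.63. All of these figures describe the interrupted schedule, not the one released.

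**The case against.** The case on the other side has real weight.

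- **Purpose.** The stated aim is to prevent treatment breaks, not to detect colitis, so it would be too strong to say that the cohort was created to catch it. That stands. The safety-cohort label and the conditional sentence still make the cohort a toxicity check.
- **Meaning of unexpected.** The lists carry no grades, so *unexpected* might cover unusual severity or frequency, and the full protocol may define it. A reader might infer that three cases of severe colitis would certainly leave escalation unchanged. The article does not support that certainty. What it supports is that the plain reading points that way and nothing in the text rules it out.
- **Exposure.** Cisplatin and radiation are given in full. The article argues from pembrolizumab's long half-life that "pembrolizumab has to be present when Cis-RT is given", and a cycle 1 dose leaves some drug present. At 32 fractions the day 43 dose overlaps only two treatment days. So it would be wrong to say that the cohort misses most of the concurrent regimen. The omission is two of three concurrent pembrolizumab doses, and repeated concurrent dosing goes untested in these patients.
- **Rates.** A reader might put the 34% grade 3 rate from the Discussion into the 0-of-3 calculation. That figure is for ipilimumab with hypofractionated radiotherapy. The same section gives 6% for pembrolizumab with radiotherapy, where P(0 of 3) = 0.94³ = 0.83. Neither is a rate for this combination.
- **Other patients.** A reader might see the ungated recurrent or metastatic patients as an oversight. Study procedures limits the interrupted schedule to locally advanced, unresectable disease, so this is an explicit choice.
- **Individual protection.** Tables 3 and 4 set management for individual severe events, and locally treated patients have day 1 and weekly assessments. That also stands, and it limits the severity of the point. It does not settle the decision at cohort level.

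**Conclusion.** The point holds, as a should-fix. The article contradicts itself on whether release is conditional. On a plain reading, its criterion does not respond to the toxicity that it gives as the reason for the cohort. The three patients omit two of the three pembrolizumab doses given during chemoradiation under the schedule being released, so a clean cohort carries limited information about that schedule. Even if the events counted, 0 of 3 would be compatible with a true rate of up to 63% (one-sided 95%).

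The conclusion rests on the rule as worded in this article and, for the dose count, on unbroken radiation from cycle 1 day 1. A definition of *unexpected* in the full protocol could resolve the second difficulty, but not the third; the unconditional wording in the other three sections would still need to be aligned.

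A reader might go further and infer that the primary analysis is compromised because it includes these three patients. The article does not support this. Its analysis set is patients treated on protocol, which includes them, and the stated power is correct.

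**What to change.** 1. Reconcile the Abstract, Aim and study design, Study procedures, and Expected toxicities and management so that they agree on whether the fourth and later locally advanced or unresectable patients are conditional on the first three.
2. State whether the severe diarrhoea and suspected colitis named as the reason for the cohort count towards release. The clinical team sets the criterion; none is proposed here.
3. Do not describe a clean cohort as establishing tolerability of the uninterrupted schedule.
4. Tabulate toxicity separately for the interrupted and uninterrupted schedules. ORR without the three patients is an optional sensitivity analysis, and the primary analysis stays as planned.

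The cost is a wording change and one extra table. If release is confirmed as conditional, enrolment in this category may pause briefly while the first three are assessed. Sample size and the primary test do not change.
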